#### 3.2 Secondary Objectives

1. Aim: to investigate differences in quality of life (QoL) and condition-specific health-related QoL, bother of pelvic floor symptoms, leakage episodes, use of continence pads, global impression of change and the proportion that met or exceeded MCIDs for the primary outcome [35] (secondary outcomes) between the telehealth-delivered pelvic floor muscle training program incorporating a novel biofeedback device and usual care.
2. Aim: to evaluate processes within this trial that, if found to be effective, will assist future translation of the findings into clinical practice, relating to fidelity, reach, effectiveness, adoption, implementation and maintenance of the intervention.
3. Mechanistic aim: to investigate if the intervention improves pelvic floor muscle strength in women in the intervention arm, at 17-weeks.
4. Aim: To assess differences in the primary and secondary outcomes at 52-weeks (secondary time point) to assess any maintenance in treatment effect.
5. Aim: To assess cost effectiveness at 52-weeks if clinical effectiveness at 17-weeks is demonstrated.

6. Aim: To conduct an exploratory analysis of whether the effects of the intervention are moderated by pre-specified moderators (radiotherapy: categorical variable [yes(type)/no]; BMI: continuous variable).

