| Primary Outcomes                                                                                                   |                                                                                                                                                                                                                                                                                                                                                                                 |                                                                                                                                                                                                                                                                          |                           |                                                                                                                          |
| International Consultation on Incontinence Questionnaire: Urinary Incontinence – Short Form (ICIQ-UI SF) [34]             | A 3-item self-reported questionnaire capturing frequency, severity and bother of any type of urinary incontinence in the past 4 weeks. Scored by summing the responses to 3-items. Items are summed to create one overall score.                                                                                                                                                | Ranges from 0-21. Higher scores indicate greater impact of UI.                                                                                                                                                                                                           | Baseline, 17 and 52 weeks | Constrained longitudinal data analysis across all time points, accounting for stratification factor and physiotherapist. |

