|                                                                          | Each item is scored on a 7-point Likert scale ranging from 1-7.

Items are summed to create one score for each domain.                                                                     |                                                                                                                                                                                                                                                                             |                           |                                                                                                                                                |
| Number and severity of leakage episodes                                  | Collected by the participant in a custom-developed 7-day Accident Diary.                                                                                                                         | Whole numbers/ counts from 0 overall and within categories of damp, wet and soaked. Reported as mean (SD) or median (IQR).                                                                                                                                                  | Baseline, 17 and 52 weeks | Poisson regression using generalised estimating equations to account for clustering, adjusting for stratification factor and physiotherapist.  |
| Number of leakage episodes by provocation                                | Collected by the participant in a custom-developed 7-day Accident Diary.                                                                                                                         | Whole numbers/counts from 0 within seven categories of provocation: i) urgency urinary incontinence, ii) stress urinary incontinence, iii) mixed urinary incontinence, iv) post-micturition leakage, v) nocturnal enuresis, vi) postural urinary incontinence, vii) unknown | Baseline, 17 and 52 weeks | Poisson regression using generalised estimating equations to account for clustering, adjusting for stratification factor and physiotherapist.  |

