The binary secondary outcomes (PGIC and physical activity category) will be compared between groups separately using logistic regression, adjusting for the stratifying variable of radiotherapy, and fit using generalized estimating equations to account for clustering, with results reported as risk ratios and risk differences. Poisson regression models fitted using generalized estimating equations will be used for secondary count outcomes (number of leakage episodes overall and by severity and provocation, number of continence pads used).

The economic evaluation will have a societal perspective and will assess both the cost of the intervention at 17 weeks and the cost-effectiveness and cost-utility of the intervention group *versus* the control group at 52-weeks. Quality-adjusted life years (QALYs) gained [56] for the intervention compared to control at 52 weeks will be assessed. QALYs will be calculated based on utility scores using the EQ-5D-5L [44, 45] at baseline and 52 weeks. QALYs will also be calculated using the ICIQ-LUTSqol [42], a condition specific quality of life measure, at baseline and 52 weeks. Analysis will be combined with the primary clinical outcome measure to establish the incremental cost-effectiveness ratio of the intervention. The difference in participant resource use related to incontinence (e.g. pad use, medication use, health service use) and productivity lost between baseline and 52 weeks will be compared for intervention and control groups. The association between utility gains on the EQ-5D-5L and productivity will be compared between the intervention and control groups. The 52-week economic evaluation will be reported separate from the main trial.

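### Damp-only and wet-only leakage counts have no fixed direction of benefit, so their modelled rate ratios cannot be read alone; a cumulative wet-or-soaked count would cure this

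*Protocol*

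**What the plan says.** The leakage data come from a diary: "Collected by the participant in a custom-developed 7-day Accident Diary", at baseline, 17 and 52 weeks. The row of Table 4.6 (Protocol section 4.6) on the number and severity of episodes sets the scale as "Whole numbers/ counts from 0 overall and within categories of damp, wet and soaked". The analysis column of the same row assigns "Poisson regression using generalised estimating equations to account for clustering, adjusting for stratification factor and physiotherapist".

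Section 12.2 repeats this. Its secondary count outcomes, to be fitted by Poisson GEE, include "number of leakage episodes overall and by severity and provocation, number of continence pads used". The grade counts are therefore between-arm comparisons and not only summaries.

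The objective that they serve is the first secondary aim in section 3.2, which lists "bother of pelvic floor symptoms, leakage episodes, use of continence pads, global impression of change".

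For the primary scale, Table 4.6 states which way is worse: "Ranges from 0-21. Higher scores indicate greater impact of UI". It makes no such statement for the damp or wet counts. The protocol defines no ordered score, no cumulative grade such as wet or worse, and no rule for reading the three grade results together.

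**The concern.** Read naturally, counting within categories puts each episode in exactly one grade. The grades are ordered by how heavy the leak was. If treatment turns a soaked leak into a wet one, or a wet leak into a damp one, the episode leaves the heavier count and joins the lighter one. The damp count then gains from wet and loses leaks that stop altogether, and the wet count gains from soaked and loses to damp. For these two counts the net change can have either sign while every leak is getting lighter or disappearing.

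The interpretation of two of the three modelled severity results is at stake. A damp rate ratio above 1 may reflect lighter leaks. One below 1 may reflect leaks that stopped, or leaks that became heavier. Neither can be called benefit or harm without the other grades beside it. The overall count is clear in direction but carries no severity information, so within the diary the grade counts are the only measure of severity.

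**Working it through.** The protocol gives no power, effect size or baseline distribution for the leakage counts, so there is no stated figure to reproduce. The check is on the definition. All weekly counts below are assumptions.

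**1. General result.** Let D, W and S be the weekly damp, wet and soaked counts. Suppose a proportion p of each grade moves down one step, with damp leaks disappearing.

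- Damp after = D(1 − p) + pW, a change of p(W − D)
- Wet after = W(1 − p) + pS, a change of p(S − W)
- Soaked after = S(1 − p), a change of −pS

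Damp rises if W > D, falls if W < D and is flat if they are equal. The same holds for wet, with S and W in place of W and D. Soaked can only fall.

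**2. Cumulative counts under the same shift.**

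- All episodes: change of −pD
- Wet or soaked: change of p(S − W) − pS = −pW
- Soaked: change of −pS

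None of these can rise.

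**3. Two assumed mixes, p = 0.5.**

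| Count | Heavier mix, before → after | Ratio | Milder mix, before → after | Ratio |
|---|---|---|---|---|
| Damp | 2 → 3 | 1.50 | 6 → 4.5 | 0.75 |
| Wet | 4 → 4 | 1.00 | 3 → 2 | 0.67 |
| Soaked | 4 → 2 | 0.50 | 1 → 0.5 | 0.50 |
| All | 10 → 9 | 0.90 | 10 → 7 | 0.70 |
| Wet or soaked | 8 → 6 | 0.75 | 4 → 2.5 | 0.625 |

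The same treatment action gives a damp ratio of 1.50 in one mix and 0.75 in the other. The cumulative counts fall in both.

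**4. A second route, between arms.** Because the grades are exclusive, damp rate ratio = overall rate ratio × (damp share in intervention ÷ damp share in control). Assume control shares of 30/40/30% for damp/wet/soaked and intervention shares of 60/30/10%. The share ratio for damp is 0.60 ÷ 0.30 = 2.

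- Same total: damp 1.00 × 2 = 2.00, wet 0.75, soaked 0.33
- 20% fewer leaks: damp 0.80 × 2 = 1.60, wet 0.60, soaked 0.27
- 40% fewer leaks: damp 0.60 × 2 = 1.20
- 50% fewer leaks: damp 0.50 × 2 = 1.00

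If the total falls by 20% with no change in shares, all three ratios are 0.80. So a damp ratio above 1 can accompany clear improvement, and so can one below 1.

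**The case against.** The strongest reply is that a clear answer is already in the plan. The overall count is analysed alongside the grades, fewer is better, and the first secondary aim names leakage episodes without naming severity. The soaked count also has a plain direction. In the heavier mix above, overall is 0.90 and soaked 0.50, both favouring treatment, and ratios of 1.50, 1.00 and 0.50 set side by side read as a shift to lighter leaks. Severity also enters the primary ICIQ-UI SF, whose direction is stated. The protocol nowhere labels a damp ratio above 1 as harm and bases no decision on it. Finally, a detailed analysis plan is promised and could say how the grades are to be read together.

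Most of this stands, and it limits the point. A reader might infer that any woman whose leaks become lighter is counted as worse on damp, or that the first secondary aim could come out in the wrong direction. The documents support neither inference. Damp rises only if inflow from heavier grades exceeds outflow, a soaked-to-wet change leaves damp untouched, and the overall count answers the aim.

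The reply does not remove the ambiguity of the damp and wet models themselves. The protocol specifies them in two places as between-arm comparisons. An analysis plan that only added an ordered summary would leave them as specified outcomes.

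**Conclusion.** The point holds as a modest one. The damp and wet rate ratios have no fixed direction of benefit and should not be reported as stand-alone treatment comparisons. The size of the distortion cannot be stated for this trial, because the baseline mix of grades is not given. Under the assumed mixes, with treatment working, the damp ratio ran from 0.75 to 2.00.

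The conclusion rests on two readings: that each episode is recorded in one grade only, and that lighter leaks count as improvement. It does not touch the ICIQ-UI SF analysis, the sample size, the overall leakage-episode comparison or the soaked comparison. It is a low-cost improvement to one secondary outcome.

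**What to change.** In Table 4.6 and section 12.2:

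- keep the Poisson GEE comparisons for all episodes and for soaked episodes;
- replace the damp-only and wet-only comparisons with one for episodes that were wet or soaked;
- state that a lower count is better for each of the three;
- report the damp, wet and soaked split by arm and time-point as a descriptive table.

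The only new modelled quantity is the wet-or-soaked count, which is the sum of two counts already collected. Modelled leakage comparisons on this row fall from four (overall, damp, wet, soaked) to three. The diary, the time-points and the method do not change. The cost is wording, and it should be settled before the analysis plan is published and allocation is unblinded, so that the choice cannot depend on results. A weighted score or an ordinal model would also fix the direction, but it would need weights or a model that the protocol does not now contain.

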| Number of continence pads used                                           | Collected by the participant in a custom-developed 7-day Accident Diary.                                                                                                                         | Whole numbers/ counts from 0. Reported as mean (SD) or median (IQR).                                                                                                                                                                                                        | Baseline, 17 and 52 weeks | Poisson regression using generalised estimating equations to account for clustering, adjusting for stratification factor and physiotherapist.  |
| Patient Global Impression of Change (PGIC) Global Rating of Change Scale | Self-reported in response to “Compared to your first assessment in this study (when you completed your baseline information 17 weeks ago) overall, how would you rate your bladder control now?” | Participants indicating they are “much improved” or “very much improved” will be classified as improved. All other respondents will be classified as not improved.                                                                                                          | 17 and 52 weeks           | Logistic regression using generalised estimating equations to account for clustering, adjusting for stratification factor and physiotherapist. |

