### 8.2 Telehealth-delivered pelvic floor muscle training program (Intervention)

Participants in the intervention group receive the same handouts as the control plus an intensive 16-week physiotherapist-supervised telehealth-delivered PFMT intervention. Pelvic floor muscle exercise will be supported by a Therapeutic Goods Administration (TGA) approved femfit® biofeedback device[53]. Directly after randomisation, a research team member will schedule each participant for their first telehealth-delivered physiotherapy consultation. The aim will be for the initial consultation to be within 2 weeks of baseline assessments. Subsequent tele-health appointments will be made by the treating study physiotherapist in consultation with the woman. Prior to a participant's first physiotherapy consultation, a member of the research team will schedule and conduct a teleconference consultation with the participant to practise the technical aspects of internet connection and screen sharing (approximately 15 – 30 minutes). Twenty-four hours prior to the participant's first telehealth-delivered physiotherapy consultation, a member of the research team will send a consultation reminder via mobile phone text message to the participant.

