### 12.2 Statistical Analysis Plan

All analyses will be described *a priori* in a detailed Statistical Analysis Plan and published while biostatisticians are blinded to treatment allocation. Demographic and baseline characteristics of participants will be summarised as appropriate (means and standard deviations for continuous variables that appear to be distributed approximately symmetrically, medians and interquartile ranges for other continuous variables, counts and percentages for categorical variables). Main comparative analyses between groups will be performed using intention-to-treat. Constrained longitudinal data analysis will be used to analyse continuous outcomes, including the primary outcome. The response will consist of all continuous outcomes (baseline, 17 weeks and 52 weeks) and the model will include factors representing treatment group, time (categorical), and a group-by-time interaction, with the restriction of a common baseline mean across treatment groups. Models will include the stratification

variable (radiotherapy) and random effects for physiotherapist (intervention arm only). The mean change in urinary incontinence (primary outcome) and other continuous outcomes (ICIQ-LUTSqol, PFBQ, EQ-5D-5L, UTAUT-II domains 1-9, METminutes (walking, moderate-intensity activities, vigorous-intensity activities) from baseline to each follow-up time-point between the two intervention groups will be obtained. The primary hypothesis will be evaluated by obtaining the estimated differences between the two intervention arms in mean change in urinary incontinence score from baseline to 17-weeks post-commencement of treatment (primary time point), two-sided 95% confidence intervals and p-values. These models provide valid inference in the presence of missing data if the data are missing at random. Standard diagnostic plots will be used to check model assumptions. Treatment effects at 52 weeks post-randomisation (secondary time point) will be estimated to assess maintenance of treatment effects for all outcomes except UTAUT-II domains 1-9 for which only 17-week follow-up data will be collected.

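### Table 4.6 gives one PGIC wording that dates baseline at 17 weeks ago but schedules the item at 52 weeks too, where that interval is wrong by about 35 weeks

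*Protocol*

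**What the plan says.** The PGIC row of the table in Protocol section 4.6 opens the item with "Compared to your first assessment in this study (when you completed your baseline information 17 weeks ago"; the parenthesis and the question that follows it read "when you completed your baseline information 17 weeks ago) overall, how would you rate your bladder control now". No other wording is given, and the time-points column reads "17 and 52 weeks". Women who choose one of the two strongest improvement categories count as improved. For the rest, the rule is "All other respondents will be classified as not improved", and that includes anyone who reports no change.

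The 52-week result has a stated purpose. Aim 4 in section 3.2 is "To assess differences in the primary and secondary outcomes at 52-weeks (secondary time point) to assess any maintenance in treatment effect". Section 12.2 repeats it: "Treatment effects at 52 weeks post-randomisation (secondary time point) will be estimated to assess maintenance of treatment effects for all outcomes except UTAUT-II", with no exception for the PGIC. The same section makes the PGIC a formal between-group comparison: "The binary secondary outcomes (PGIC and physical activity category) will be compared between groups separately using logistic regression", reported as risk ratios and risk differences.

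Section 8.2 describes the treatment as "an intensive 16-week physiotherapist-supervised telehealth-delivered PFMT intervention", with the first consultation intended within two weeks of baseline. Section 5.7 ends follow-up 52 weeks after randomisation.

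**The concern.** A global change item has no score of its own at each visit. It asks only for change against a reference point, so the reference point defines the outcome. At 17 weeks the printed interval and the named comparator agree closely. At 52 weeks they do not: the first assessment was about a year earlier, while the parenthesis says 17 weeks.

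The 52-week PGIC is part of the evidence on whether the effect lasts. If some women answer against the printed interval, their answers describe change since a date after treatment ended. Improvement gained during the programme and held since then would not register. A fall in the proportion improved between 17 and 52 weeks could then come partly from the wording and be read as loss of effect.

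**Working it through.** The plan states no figure for this point, so there is none to reproduce. The check is date arithmetic followed by an illustration.

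**Dates, in weeks from baseline**

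- Inputs: assessment at week 52 (section 5.7, taking randomisation as close to baseline); printed interval 17 weeks (section 4.6); programme 16 weeks, starting 0 to 2 weeks after baseline (section 8.2).
- Date implied by the printed interval: 52 − 17 = week 35.
- Error in the interval: 52 − 17 = 35 weeks.
- End of treatment: 16 + 0 = week 16, to 16 + 2 = week 18.
- Gap from end of treatment to the implied date: 35 − 18 = 17 weeks, to 35 − 16 = 19 weeks.
- At the primary time-point, 17 weeks after treatment starts, baseline lies 17 + 0 = 17 to 17 + 2 = 19 weeks back. The mismatch there is at most about two weeks.

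**How one answer changes**

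Take a woman who improved greatly by the end of treatment and stayed the same. Against her first assessment she is much improved and is coded improved. Against week 35 she is unchanged and is coded not improved.

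**Illustration of size**

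Assume 67% improved with training and 29% with control. These are the rates of cure or improvement for any urinary incontinence quoted in section 2.2. They come from another population and are not PGIC rates, so they serve only as an example. Assume also that all improvement was gained before week 35 and held. Let a share f of women in each arm follow the literal date.

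Risk difference = (67 − 29) × (1 − f) = 38 × (1 − f) points.

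| f | Training | Control | Risk difference |
|---|---|---|---|
| 0 | 67.0% | 29.0% | 38.0 points |
| 0.10 | 60.3% | 26.1% | 34.2 points |
| 0.25 | 50.3% | 21.8% | 28.5 points |
| 0.50 | 33.5% | 14.5% | 19.0 points |

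Two limits of this model matter.

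- With equal f, the crude risk ratio stays at 67/29 = 2.31 for any f below 1, because (1 − f) cancels. The risk difference shrinks; the ratio does not.
- Equal f is itself an assumption. If only a quarter of the training arm follows the literal date, the difference is 67 × 0.75 − 29 = 21.25 points. If only a quarter of the control arm does, it is 67 − 29 × 0.75 = 45.25 points.

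The protocol gives no basis for f in either arm.

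**The case against.** The strongest reply is that the item names its comparator. It begins with the woman's first assessment in the study and describes it again as the time she completed her baseline information. The 17 weeks only dates that event. No baseline questionnaire was completed at week 35, so a woman who reads the whole sentence has a clear event to compare with. This stands. A reader might infer that the item cannot measure change from baseline at 52 weeks, or that it simply refers to a date after treatment. The documents do not support that: the item is mis-dated and ambiguous at 52 weeks, but it still names baseline. The lead phrase does not remove the conflict, however. By 52 weeks each woman has also been asked for a 17-week assessment, so the number could cue that visit instead.

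A second reply is that the wording in use at 52 weeks cannot be seen. The modification log shows that the 52-week questionnaire is its own booklet, with its own PGIC section, and that it has been edited separately from the 17-week booklet. The table row may simply quote the 17-week form. This also stands. It cannot be said that any woman has received the wrong wording.

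A third reply is that the bias is not demonstrated. A reader might infer that the 52-week result is biased toward no change. That needs women to set aside the named comparator and to have been stable since week 35, and neither is established. Attenuation is the plausible direction if benefit is gained during treatment and held, since the literal reading removes improvement made before week 35. Unequal shares between the arms could alter that.

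Finally, maintenance is also assessed with the ICIQ-UI SF, ICIQ-LUTSqol, PFBQ, leakage episodes and pad use, none of which depends on this item. That limits the consequence.

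**Conclusion.** The point holds as a wording error with a conditional consequence. As written, table 4.6 prints an interval that is right at 17 weeks and wrong by about 35 weeks at 52 weeks, where it conflicts with the comparator named in the same sentence. If the effect is maintained and some women answer by the printed interval, the 52-week PGIC comparison could be attenuated. The amount cannot be estimated from the protocol: it is nil if women answer against the first assessment, and the figures above depend on borrowed rates and an assumed share.

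The reach is one binary secondary outcome at the secondary time-point. The primary outcome, the sample size and the significance level are untouched, and the 17-week PGIC is essentially unaffected. A reader might conclude that the 52-week PGIC should be dropped as evidence on maintenance. The documents do not justify that, because the item still names baseline and the booklet wording is unknown. The error is nevertheless worth correcting, since the trial relies on the item for a stated aim and the correction is one line.

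**What to change.** 1. In table 4.6, give the PGIC a separate 52-week wording that keeps the first assessment as comparator and either drops the interval or states the right one, for example about 12 months ago or the woman's actual baseline date.
2. Check the PGIC section of the 52-week booklet against the table. Correct it if it repeats 17 weeks; if it is already right, only the table needs changing.
3. If any women have already been given the wrong interval at 52 weeks, record which wording each received. Add a sensitivity analysis of the 52-week PGIC by wording, and keep the outcome in the maintenance analysis.

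The cost is a one-line text change and, if the booklet is affected, a minor ethics notification. The document is dated July 2024 and section 4.5 expects data collection to run to June 2025, so on that timetable some 52-week questionnaires were still to be sent. The small downside is that two wordings may exist among women already assessed, and with 72 women planned the sensitivity analysis will be imprecise.
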